Among the selected points, LI11, TE5, LI4, PC6, HT1, and LU5 will be needled unilaterally based on the affected side of the patient. HT1 will be needled at 45°–90° to the body surface and inserted to a depth of 0.3–0.5 cun. TE5, LI4, and PC6 will be needled at 90° to the body surface and inserted to a depth of 0.5–1.0 cun. LI11 and LU5 will be needled at 90° to the body surface and inserted to a depth of 1.0–1.5 cun. Temporal three needles will be needled at 15°–30° to the body surface and inserted to a depth of 0.3–0.5 cun. Following insertion, stimulation of the acupuncture point will be performed with bidirectional rotation of the needle sleeve at approximately 18–300 per min. The acupuncture manipulation will be adjusted according to the tolerance of each patient with the methods of tonifying and purging to achieve the feeling of “deqi” without obvious pain. The needles will be maintained in place for 30 min. A sterilized, dry cotton ball will be gently pressed against the point to prevent bleeding when each needle is withdrawn. The entire course of treatment will occur over 30 min, while the upper limbs will be treated with MT.

During MT, patients who pass the kinesthetic and visual imagery questionnaire (KVIQ) test will sit close to the table. A 5 cm × 35 cm mirror will be placed vertically between the upper limbs on the table, with the reflecting surface facing the uninjured limb. Patients will be asked to observe the motion of the upper limb on the uninjured side and imagine that the limb on the affected side was in motion, imagine the motion of the affected limb the same as that observed on the uninjured side, and complete 6 movements including shoulder joint forward flexion, elbow joint flexion and extension, forearm forward and backward rotation, wrist joint flexion and extension, finger extension and grasping, and thumb abduction. The participants will be asked to perform each movement for 5 min and try to reach the maximum range of motion of the joints. Training will be completed for 30 min per day.

For the period of treatment, acupuncture and mirror training were performed 6 times per week for 4 weeks.

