#### Primary outcomes

The primary outcomes in this study are the mean change in the scores on the FMA-UE from baseline to 4 weeks intervention and 12 weeks follow-up, as well as fMRI between the two groups and within groups from baseline to 4 weeks intervention.

FMA-UE is widely used for motor function assessment and can reflect the functional level of stroke subjects. The upper extremity has a maximum score of 66 points divided into three parts, namely shoulder arm (36 points), wrist hand (24 points), and coordination (6 points) and higher score indicate better upper limb movement function [4]. The FMA-UE is the most common scale for evaluating upper limb motor function after CIS. It is often used as a gold standard for testing the validity of other scales as well [26, 27]. The FMA-UE has excellent reliability and validity and is sensitive enough for clinical and research practice [28].

fMRI is a noninterventional imaging technique that uses magnetic resonance to measure changes in brain hemodynamics caused by neuronal activity as a reflection of the activation state of brain areas. For the observation methods, after the patients are ready, scanning will be performed on the whole brain of the patients. During resting-state scanning, patients will be instructed to relax, close their eyes, and avoid systematic thinking activities as much as possible. After resting-state scanning for 6 min, functional state scanning will be performed. The experimental task will be designed in blocks. There will be 10 trials for each task state (Fig. 3), and the time of each trial is 30 s. In addition, there are 10-s empty sweeps before each scan, so each scan is 5 min and 10 s. Once in place, the subjects will be put on noise-canceling earphones and receive instructions. Patients will be asked to try to imagine their fingers flexing when they hear the word “close.” When they hear the word “open,” they will be asked to try to imagine their fingers straightening. Each subject will receive task training in advance.

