A related study [36] indicated that traditional acupuncture therapy combined with modern rehabilitation training can significantly promote the recovery of limb function in patients with CIS, especially the distal joint. In this study, JTN combined with MT activated relevant sensory areas in the brain through visual feedback to improve the overall motor function of patients. It was concluded that mirror neurons in the brain were directly involved in the imitation and understanding of movements under the action of image stimulation, and the brain-damaged areas of motor function in patients with paraplegia were reorganized to compensate for the loss of motor function.

The fMRI results before and after treatment will be used as the reference for clinical efficacy evaluation in this study to provide valuable information on the changes in neuronal activity in local brain areas caused by CIS and information on the node attributes in the functional connectivity group.

However, the efficacies of JTN and MT have not been systematically compared, and any possible synergistic effect of their combination has not been evaluated. Therefore, we propose a rigorous, randomized, controlled clinical trial to test whether the two treatment methods applied in combination are more effective than the single method. In this study, we will systematically evaluate the effects of different treatments on upper limb motor dysfunction after CIS and assess upper limb motor function and daily activity. The long-term stability in the improvements will also be evaluated during a 12-week follow-up examination after the intervention.

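### The fMRI imagery task resembles training given only to the JTN+MT arm, so a between-arm difference in task activation cannot serve as the reference for clinical efficacy

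*Protocol article*

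**What the plan says.** **Status of fMRI.** Under Primary outcomes, the protocol article lists the change in FMA-UE and adds "as well as fMRI between the two groups and within groups from baseline to 4 weeks intervention". The Abstract differs: it names an FMA-UE effective rate as primary and puts the fMRI analyses among the other measures.

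**What is scanned.** Primary outcomes describes two parts: "After resting-state scanning for 6 min, functional state scanning will be performed". The functional part is imagery in response to spoken cues: "Patients will be asked to try to imagine their fingers flexing when they hear the word" close, and straightening on open. It adds: "Each subject will receive task training in advance".

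**What the JTN+MT arm trains.** In the section on the JTN combined with MT group, patients watch the uninjured limb in the mirror and "imagine the motion of the affected limb the same as that observed on the uninjured side". The six movements end with "finger extension and grasping, and thumb abduction". On duration: "The participants will be asked to perform each movement for 5 min". Sessions take place 6 times per week for 4 weeks.

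**What the JTN arm receives.** The JTN group section gives the same acupuncture and describes no mirror, imagery or other counterpart.

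**How fMRI will be used.** The Discussion states: "The fMRI results before and after treatment will be used as the reference for clinical efficacy evaluation in this study". The Conclusion assigns fMRI to the central mechanisms of the effects.

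**The concern.** The trial asks whether adding mirror therapy improves arm function and, through fMRI, by what central mechanism. The task scan asks something narrower: whether the arms differ in activation while imagining finger movement. One arm has spent four weeks rehearsing something close to that task by the second scan, and the other arm has not.

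A difference in task activation therefore has at least two explanations. The motor system may have reorganised along with recovery of the arm, or patients who practised imagery may simply respond differently to an imagery task. The second needs no difference in arm function. If fMRI is taken as the reference for efficacy, a significant task result could be reported as support for clinical benefit, or as the mechanism of motor recovery, although the scan contrast alone cannot separate the two explanations.

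**Working it through.** **1. Is the overlap in the text?**

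| Element | Scanner task | Mirror therapy (JTN+MT only) | JTN arm |
|---|---|---|---|
| Mental activity | imagined movement | imagined movement of the affected limb | none described |
| Movement | finger flexion and straightening | finger extension and grasping, 1 of 6 movements | none described |
| Cue and setting | spoken word, no mirror described | mirror view, with movement of the uninjured limb | not applicable |

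The two are close but not identical.

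**2. Exposure before the second scan.**
- Sessions: 6 per week x 4 weeks = 24.
- Finger extension and grasping: 24 x 5 min = 120 min in JTN+MT, 0 min in JTN by protocol.
- All mirror therapy: 24 x 30 min = 720 min.

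These minutes mix imagery, mirror viewing and executed movement of the uninjured limb. They are not minutes of pure imagery.

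**3. Does anything offset it?** A normal imagery questionnaire at entry and task training in advance apply to both arms. They make the arms alike before treatment but do not equalise four weeks of practice in one arm. Assessor blinding does not alter the patient's own response in the scanner. No executed or unrehearsed task is described. The resting-state scan involves no instructed imagery, so the direct overlap does not apply to it.

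**4. Numbers per arm.** The plan's own figure can be reproduced. With effective rates of 88.9% and 56.1%, two-sided 0.05 and power 0.80, the unpooled normal formula gives

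n = (0.889 x 0.111 + 0.561 x 0.439) x (1.960 + 0.842)^2 / 0.328^2 = 25.2, rounded up to 26 per arm.

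The plan enrols 30 per arm. The point does not depend on this calculation; it only supplies 26 and 30 for step 5.

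**5. How readily could practice alone show as a difference?** The documents give no practice-effect size, so a range d (in SD units) is assumed, with no arm difference in motor recovery. The fMRI measure is treated as one number per patient and compared by a two-sided t test at 0.05. That is also an assumption, because the article states no fMRI test. The rejection probability comes from the noncentral t distribution with 2n - 2 degrees of freedom and noncentrality d x sqrt(n/2). For example, at n = 30 and d = 0.5, the noncentrality is 0.5 x sqrt(15) = 1.94 and the critical value is 2.00, which gives 48%.

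| Assumed shift d | 30 per arm | 26 per arm |
|---|---|---|
| 0.1 | 6.7% | 6.4% |
| 0.2 | 12% | 11% |
| 0.3 | 21% | 19% |
| 0.5 | 48% | 42% |
| 0.8 | 86% | 81% |

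These figures are power to detect a true activation shift. They show that such a result is possible without recovery and that its probability depends heavily on an unknown. They do not show that it is likely.

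**The case against.** The strongest reply is that imagery is part of the treatment and not a contaminant. The Discussion describes mirror therapy as including motor imagination intended to promote restructuring of brain function. Activation that changes because imagery was trained is a randomised effect of allocation, and probing a therapy's trained network with a related task is a defensible mechanistic choice. This stands. The task need not be dropped, and a difference would be a legitimate finding about what the therapy does to the brain.

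A reader might infer that the false-positive rate exceeds 0.05. The documents do not support that: if practice shifts activation, the null of equal activation is false and rejecting it is correct. The error would lie in the inference from activation to recovery, not in the size of the test.

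A reader might also infer that the whole fMRI outcome is compromised. The article says only fMRI, includes a resting scan, and mentions connectivity in the Discussion. The overlap concerns the task part.

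Finally, the efficacy role rests on one Discussion sentence, which goes on to speak of information on neuronal activity. No decision rule lets fMRI establish efficacy, and FMA-UE is assessed separately by blinded assessors. This limits the harm. The sentence still gives fMRI a role in judging efficacy, and Primary outcomes places it beside FMA-UE.

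**Conclusion.** The point holds as a limit on what the trial may conclude. The task contrast resembles training received in one arm only, so a between-arm difference could arise from imagery practice without any difference in arm recovery. It cannot serve as the reference for clinical efficacy, and alone it does not show the mechanism of motor recovery.

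The firm quantity is the exposure: 120 min of mixed training in finger extension and grasping against none. The chance that practice alone gives a significant task result ranges from about 7% to 86% with 30 per arm. That range rests entirely on assumed shifts of 0.1 to 0.8 SD and an assumed t test on a single summary measure. FMA-UE is not an imagery task, so its comparison is untouched by this overlap.

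**What to change.** - **Discussion:** remove the statement that fMRI is the reference for evaluating clinical efficacy.
- **Primary outcomes:** state that the efficacy conclusion rests on the between-group FMA-UE comparison only and that fMRI is a mechanistic outcome. This also agrees with the Abstract, which lists fMRI among the other measures.
- **Reporting:** present the imagery-task contrast as the response to a task resembling the training in one arm, and state that it is not by itself evidence of motor recovery. Report the resting-state scan alongside as the measure without instructed imagery, without claiming that it is free of training effects, since 24 sessions could also alter resting connectivity.

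Making the resting scan the primary fMRI measure, or requiring an association between change in activation and change in FMA-UE, is not needed. Neither would establish mechanism: the second relates two changes that both occur after randomisation.

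The cost is wording only, with no new scans, patients or staff. The downside is that fMRI loses its status as a primary efficacy outcome.

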**Fig. 3 Fig3:**

Task flowchart. R, rest; T, task

#### Secondary outcomes

The mean changes in the scores on the MAS, ARAT, and ADL before and after 4 weeks treatment as well as 12 weeks follow-up intervention are secondary outcomes.

MAS scale mainly focuses on comprehensive physical ability and muscle tension. It includes 9 items, from supine to the lateral position, from supine to sitting on the bed, seat balance, from seat to standing on foot, walking, upper limb function, hand movement, fine function of the hand, and muscle tension of the whole body. There are 7 points (0~6) for each of 9 items. Movement disorders can be divided into mild (33 points above), moderate (17~32 points), and severe (0 to 16 points) [29].

The ARAT is a standardized scale for the assessment of upper limb dysfunction after stroke. It evaluates the upper limb movement through four basic movements: grasping (6 items), gripping (4 items), pinching (6 items), and gross movements (3 items). Each project is on a 4-point scale, with 0 indicating failure and 3 indicating normal completion. Full score is 57 [4].

ADL scale includes 10 items related to bowel and bladder continence, grooming, toileting, feeding, transfer, walking, dressing, bathing, and going up and down stairs. A normal score is 100. Ability of daily life disorders can be divided into mild (61~99 points), moderate (41~60 points), severe (1~40 points), and completely dependent (0 points) [4].

### Sample size

The sample size was calculated based on the effective rate of the treatment. Based on similar previous studies [30], we assumed the effective rate of 88.9% and 56.1% in the JTN+MT group and the control group, respectively. The PASS11.0 software was used to perform a power analysis to determine the sample size. Type-1 error was assumed at 0.05, type-2 error at 0.2. The required sample size was 26 subjects for each group. Considering a dropout rate of 15%, a total of 60 subjects needed to be enrolled (30 participants per group).

### Adverse events and safety monitoring

Adverse events will be recorded and managed by researchers within 24 h. There will be at least one physician to evaluate and manage the adverse events at each center. Serious adverse and unexpected events will be reported to the Ethics Committee and other supervising departments. The subjects may leave the trial at their own discretion, or the physicians will determine whether the patient will continue or terminate the study. However, the patient will be followed up until they are in a stable condition following the adverse event.

The primary investigator will review all adverse events periodically, and the Ethics Committee and DMC will have access to the interim results. If necessary, a meeting will be held to reappraise the benefits and risk of this trial.

The possible adverse events related to acupuncture treatment include fainting during treatment, nausea, needle stuck, needle breakage, local hematoma, local infection, and viscera or peripheral nerve injury. Adverse events will be assessed based on the symptoms, frequency, and severity of the patients throughout the study. Patients who are intolerant to the treatment should be removed immediately from the trial.

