#### Concomitant treatments

The patients in two groups will be treated with basic medications in the meantime. The patients in two groups will be treated with basic medications according to guidelines for clinical management of cerebrovascular disorders [25] to control blood pressure: individual treatment is adopted to stabilize blood pressure below 135/85 mmHg or within the normal range, control blood sugar and lipid, and prevent platelet aggregation.

The patients in the two groups will be provided with instructions to discourage them from receiving any additional specific complementary treatments related to upper limb dysfunction after CI throughout the trial, including abdominal acupuncture, fire acupuncture, floating acupuncture, and other acupuncture therapies, moxibustion, herbal medicine, massage, etc. If a patient needs other prescription medication, the relevant information will be recorded in the Case Report Form for that patient. The data will be assessed by two blinded researchers, to ensure whether be included.

For follow-up, all participants will participate in a 12-week follow-up after 4 weeks intervention. At the end of a 12-week follow-up period, participants will be referred for clinical evaluation to assess their functional status, including Fugl–Meyer Assessment for Upper Extremity (FMA-UE), motor assessment scale (MAS), action research arm test (ARAT), and activities of daily living (ADL) scale.

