### Data collection and statistical analysis

Therapists will collect the data using Case Report Forms. Two independent researchers will then input the data into the database. All analyses will be carried out under the guidance of independent data monitors to ensure the security and dependability of the data. About the dropped-out participants, their number and the reason for termination will be recorded, especially for adverse events. All enrolled patients will be included in the primary analysis conducted in accordance with the intention-to-treat (ITT) principle. The data will be analyzed by SPSS for Windows version 19.0. The statistical significance is defined as a two-sided *P* value of ≤ 0.05. The baseline characteristics will be reported as the means ± standard deviation (SD). For comparison of baseline materials, a chi-squared or Fisher’s exact test will be used for categorical variables, Student’s *t* test will be used for normally distributed data, and the Mann-Whitney *U* test will be used for non-normally distributed data. The scores of each rating scale and laboratory index before the intervention will be compared between the groups via Student’s *t* test or the Mann-Whitney *U* test. For the comparison within groups, the changes in the scores and indexes from baseline to endpoint will be assessed by a paired *t* test or the Wilcoxon rank-sum test. For the difference between groups, we will use Student’s *t* test or the Mann-Whitney *U* test. For the safety analysis, the adverse events will be listed and analyzed using a chi-squared or Fisher’s exact test. For participants who discontinue or deviate from intervention, listwise deletion or multiple imputation will be used.

The data of fMRI will be analyzed by professional technicians at the Shenzhen Advanced Institute.

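### Intolerant patients are removed from the trial rather than from treatment, and the missing-data rule reaches everyone who discontinues or deviates; both are at odds with the stated ITT analysis

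*Protocol article*

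**What the plan says.** All references are to the protocol article.

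- *Adverse events and safety monitoring*, on intolerance: "Patients who are intolerant to the treatment should be removed immediately from the trial".
- The same section, on medical decisions: "the physicians will determine whether the patient will continue or terminate the study". The follow-up it then states is this: "the patient will be followed up until they are in a stable condition following the adverse event".
- *Data collection and statistical analysis*, on the analysis set: "All enrolled patients will be included in the primary analysis conducted in accordance with the intention-to-treat (ITT) principle".
- The same section, on patients who leave: "About the dropped-out participants, their number and the reason for termination will be recorded, especially for adverse events". On those who stop or depart from treatment: "For participants who discontinue or deviate from intervention, listwise deletion or multiple imputation will be used".
- *Primary outcomes*: "mean change in the scores on the FMA-UE from baseline to 4 weeks intervention and 12 weeks follow-up", together with fMRI from baseline to week 4.
- *Concomitant treatments*, on the general schedule: "all participants will participate in a 12-week follow-up after 4 weeks intervention". *Outcome measures* likewise gives the 12-week assessments to all patients.

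**The concern.** Two written rules act on the same patients.

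The first concerns conduct. Intolerance takes a patient out of the trial, and a physician's decision is likewise framed as ending the study rather than the treatment. The stated follow-up is tied to recovery from the adverse event, not to week 4 or week 16. Nothing in the article says that a removed patient still attends the outcome visits.

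The second concerns analysis. Deletion or imputation is triggered by discontinuing or deviating from intervention, not by an outcome being absent. Read literally, it would let an FMA-UE score that was measured in a patient who stopped treatment be dropped or replaced.

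An intention-to-treat analysis needs the outcomes of patients who stopped treatment. Here those outcomes may go unmeasured or unused because of an event that follows randomisation and is related to treatment. Listwise deletion leaves these patients out. Multiple imputation has to draw largely on patients who tolerated treatment. Neither method recovers a value that was never measured.

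**Working it through.** **1. The texts side by side.**

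| Question | What the article states | What it does not state |
|---|---|---|
| What does intolerance end? | Participation in the trial | That only treatment ends |
| What follow-up comes after an adverse event? | Safety follow-up until stable | That outcome visits continue, or that they stop |
| What is recorded for dropouts? | Number and reason | That nothing else is kept |
| What triggers deletion or imputation? | Discontinuing or deviating from intervention | That it is limited to missing outcomes |
| Who is analysed? | All enrolled patients, by ITT | How removed patients contribute a value |

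The general schedule covers all participants, and the removal rule covers one subgroup specifically. This is a tension, not a strict contradiction.

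**2. The plan's own figures.** *Sample size* gives 26 per group and 30 after 15% dropout. With 88.9% against 56.1%, two-sided 0.05 and power 0.80, the unpooled normal approximation gives (0.889 × 0.111 + 0.561 × 0.439) × (1.960 + 0.842)² / 0.328² = 25.17, so 26. Then 26 × 1.15 = 29.9, so 30 (26/0.85 = 30.6 would give 31). The allowance is 0.15 × 30 = 4.5 patients per arm for all causes. The article gives no intolerance rate and no expected FMA-UE gain.

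**3. Bias under complete-case deletion.** Let k be the number removed from an arm of 30, g the mean gain of those who stay and r the mean gain of those removed. The full-arm mean is g − (k/30)(g − r), so deletion overstates that arm by (k/30)(g − r). For the difference between arms (T combined, C control):

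bias = (kT/30)(gT − rT) − (kC/30)(gC − rC)

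Without assuming any gains, each point of shortfall in one arm costs 1/30 = 0.03 point for k = 1, 2/30 = 0.07 for k = 2 and 4/30 = 0.13 for k = 4. With equal removals, only the difference in shortfall between arms matters.

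**4. Illustration.** Assumed: gT = 8, gC = 5 and four removed per arm. Four is close to the planned all-cause dropout; it is not an estimate of intolerance.

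| Removed patients | Calculation | Bias (FMA-UE points) |
|---|---|---|
| Gain nothing | 1.07 − 0.67 | +0.40 |
| Lose 2 points | 1.33 − 0.93 | +0.40 |
| Gain half as much | 0.53 − 0.33 | +0.20 |
| Fall short by 4 in both arms | 0.53 − 0.53 | 0 |
| Fall short by 2 (T) and 5 (C) | 0.27 − 0.67 | −0.40 |

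With two removed per arm, each value halves. If removal were one-sided, four patients with no gain would give +1.07 (combined arm only) or −0.67 (control arm only). The formula does not describe multiple imputation.

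**5. Precision.** With equal SDs, losing 4 of 30 per arm multiplies the standard error of the difference by √(30/26) = 1.074, or 7.4% wider. That lies within the dropout already planned.

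**6. How many patients a change of conduct could reach.** *Trial status* gives recruitment from Jan. 1, 2018 to Dec. 30, 2020, a span of 1094 days; the article appeared on 2021-01-12. Assuming even recruitment, patients enrolled in the last 15 days were still before week 4: 60 × 15/1094 = 0.8. Those enrolled in the last 99 days were still before week 16: 60 × 99/1094 = 5.4.

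**The case against.** The strongest reply is that the removal sentence is loose wording in a safety paragraph. The follow-up until stable reads as a minimum duty of care, stands two paragraphs before the intolerance sentence, and forbids nothing. The general schedule assigns the 12-week assessments to everyone. Recording the number and reason for dropouts does not mean that nothing else is recorded. Listwise deletion and multiple imputation are ordinarily methods for missing values, so the authors may have meant no more than that. The article also condenses a full protocol that is not shown.

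Much of this stands, and it limits the point. A reader might infer that follow-up runs only until the event is stable and that later outcome visits are ruled out. The text does not support this: it sets a safety minimum and is silent on outcome visits. A reader might also infer a serious bias. For example, if 5 of 30 patients in one arm were removed, all non-responders and all deleted, an effective rate of 56.1% would appear as 30 × 0.561/25 = 67.3%, 11.2 percentage points too high. Nothing in the document supports one-sided removal of that size, and *Primary outcomes* names mean change, not the effective rate. The listed adverse events are acupuncture events, and *JTN group* gives both arms the same acupuncture, so roughly balanced removal is more plausible.

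What does not stand is the suggestion that there is nothing to correct. The removal rule names the trial, and a general schedule does not clearly override a specific instruction to remove a patient. An analysis plan cannot restore outcomes that were never collected. Balance is plausible but not assured: only the combined arm also has 30 minutes of mirror training at each session, and patients and acupuncturists know the allocation.

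**Conclusion.** The point holds as a badly fixed rule, not as missing detail. The safety section removes intolerant patients from the trial rather than from treatment, and states only safety follow-up without providing for or forbidding later outcome visits. The analysis section applies deletion or imputation to everyone who discontinues or deviates. Followed as written, the two can lose or discard week-4 and week-16 FMA-UE and week-4 fMRI, which is at odds with the stated ITT analysis.

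The size and direction of any bias are unknown. It is probably small if removals are balanced: between −0.4 and +0.4 points on a 66-point scale in the balanced illustrations. Those figures rest on assumed gains of 8 and 5, four removals per arm and complete-case deletion. They are illustrations, not bounds. The point deserves a correction because the correction is cheap, not because large harm has been shown.

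**What to change.** In *Adverse events and safety monitoring*, state that intolerance or a physician's decision ends study treatment only; the clinical stopping decision itself is unchanged. Keep the scheduled week-4 and week-16 FMA-UE, MAS, ARAT and ADL, and the week-4 fMRI and safety tests, where clinically feasible, unless the patient withdraws consent to follow-up. Record stopping treatment separately from leaving the trial, with dates.

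In *Data collection and statistical analysis*, use every observed outcome from patients who stopped or deviated from treatment, and restrict imputation or deletion to outcomes that are actually missing. Report the number removed in each arm and which assessments were obtained from them, including patients already removed.

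The cost is one reworded sentence, one clarification, one case report form item, a few return visits that are already on the schedule, and the notice to the ethics committee and registry that *Ethics and dissemination* requires. With recruitment due to end on Dec. 30, 2020, the change in conduct could reach few patients by publication. The analysis rule and the per-arm reporting apply to all 60 and are the main remaining gain.
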